### Outcome definitions

For an overview of the clinical endpoints in this study we refer to Table 3.

**Table 3 Tab3:** Clinical endpoints LESS-CoV-2 study

*Primary endpoint*	
Incidence (per person-year) of COVID-19 in a two-years period after SARS-CoV-2 vaccination in patients with CKD stage G4-G5 or on KRT.	
*Secondary endpoints*	
Efficacy	
• The antibody based immune response to SARS-CoV-2 vaccination at 28 days after SARS-CoV-2 vaccination.	
• The durability of the antibody response at 6 months after SARS-CoV-2 vaccination	
Safety	
• Incidence of mortality	
• Incidence of AEs of specific interest as defined by (inter) national authorities	
• Incidence of a combined endpoint of acute rejection or graft failure in kidney transplant recipients	
• Incidence of HLA antibodies defined as cPRA > 5% in dialysis patients on the waiting list for their first kidney transplantation	
*Exploratory endpoints*	
Vaccination coverage rates	
Disease severity in patients who develop COVID-19, assessed as	
• Hospitalization	
• ICU admission	
• Mechanical ventilation	
PROMs in patients on dialysis	
SARS-CoV2 genotype in patients with COVID-19 (in case available)	

*COVID-19* Coronavirus Disease 2019, *SARS-CoV-2* Severe Acute Respiratory Syndrome Coronavirus-2, *CKD* Chronic Kidney Disease, *KRT* Kidney Replacement Therapy, *AEs* Adverse Events, *HLA* Human Leukocyte Antigen, *cPRA* Calculated Panel Reactive Antibody, *ICU* Intensive Care Unit, *PROMs* Patient Reported Outcome Measures

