### Antibody measurement

We will analyse the presence of antibodies against the RBD of the SARS-CoV-2 S-protein (IgG anti-RBD antibody) using the Sanquin anti-SARS-CoV-2 RBD IgG ELISA assay [15]. This is an indirect ELISA using microtiter plates coated with RBD and detection by monoclonal mouse anti-human IgG. The antibodies against the RBD are the primary constituent of the humoral immune response after SARS-CoV-2 vaccination. We combine this test with a Sanquin anti-SARS-CoV-2 nucleocapsid protein (NP) bridging ELISA. This test is an indirect ELISA using microtiter plates coated with NP and detection by biotin-labelled NP. Both antibodies against RBD and NP arise after a natural COVID-19 infection. In contrast, vaccination only induces antibodies to RBD, since NP is not part of any of the currently used vaccines. Combining these two tests enables us to differentiate between antibodies after vaccination or after previous COVID-19 infection.

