#### Analysis of primary endpoint

Incidence rates of COVID-19 within 2 years after vaccination will be reported for each study population separately and incidence rates will be compared. Primary comparisons are comparisons of COVID-19 incidence rates in vaccinated patients versus non-vaccinated patients and versus the vaccinated general population. These comparisons will be made separately for patients with CKD stages G4-G5 or on KRT. For comparison of incidence rates, we will calculate crude hazard ratios. Vaccine efficacy will be reported as 100 × (1- hazard ratio). We will calculate model adjusted hazard ratios using multivariable Cox-regression, in case of imbalance in study populations regarding relevant characteristics, such as age, sex, comorbidity, kidney replacement modality and use of immunosuppressive agents. Cause specific hazard ratios will be estimated to account for competing risk of mortality. Starting date of follow-up will be the date of second vaccination in vaccinated patients. Starting date of follow-up in non-vaccinated patients will be the same date (or +/− 7 days from date of vaccination) as date of vaccination in the matched vaccinated patients to account for changes in incidence of COVID-19 over time. Non-vaccinated patients will be censored at the day of vaccination in case they are vaccinated before the end of follow-up. The aforementioned analyses will be repeated in patients with and patients without evidence of prior infection. Among vaccinated patients, incidence rates will also be compared across the various vaccines that will be used. For this purpose, vaccinated patients with CKD stages G4-G5 or on KRT and general population again will be analysed separately.

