#### Analysis of secondary endpoints

##### Efficacy - Antibody response

Participants will be classified as responders or non-responders [17]. Number and proportion of responders and non-responders at day 28 will be reported for each patient population. Pearson chi-2 test will be performed to assess whether antibody response differ between patient groups. In subsequent sensitivity analyses we will perform multiple regression analyses correcting for possible differences in age and sex between the patient groups. Additionally, in kidney transplant recipients we will investigate whether time after transplantation, and the different immunosuppressive regimens are associated with response rate.

To assess durability of response within each patient group, we will report and compare response at day 28 with response at month 6 after vaccination. Comparison will be made using McNemar test.

The association between antibody response after SARS-CoV-2 vaccination and protection against COVID-19 will be examined for each patient group separately. For this, we will compare the antibody response at 28 days after vaccination in patients who develop COVID-19 with the antibody response in patients who did not develop COVID-19. Similar comparison will be made at 6 months after vaccination. We will examine this by use of the t-test or if more appropriate a non-parametric test. Subsequently, in a logistic regression model using Youden’s index, a cut-off in the antibody response at 28 days will be defined to serve as a correlate of protection against COVID-19.

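### The month-6 comparison of antibody level by COVID-19 status does not require infection to follow the sample, so infection-affected titres bias the association towards no protection

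*Protocol article*

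**What the plan says.** All references are to the protocol article.

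- **Efficacy - Antibody response.** For each patient group, "we will compare the antibody response at 28 days after vaccination in patients who develop COVID-19" with that in patients who did not. The next sentence extends this to the later sample: "Similar comparison will be made at 6 months after vaccination". The method is fixed: "We will examine this by use of the t-test or if more appropriate a non-parametric test". A logistic model with Youden's index follows, in which "a cut-off in the antibody response at 28 days will be defined to serve as a correlate of protection against COVID-19". Only the day-28 sample feeds the cut-off.
- **Analysis of primary endpoint.** "Starting date of follow-up will be the date of second vaccination in vaccinated patients". No other start of case counting for vaccinated patients appears. The repeat of analyses by prior infection is placed here, for the primary endpoint.
- **Outcome definitions, Table 3.** The outcome is "Incidence (per person-year) of COVID-19 in a two-years period after SARS-CoV-2 vaccination".
- **Study design.** Samples are taken 28 days and 6 months after the second dose, so both fall inside the period in which COVID-19 is counted.
- **Antibody measurement.** "Both antibodies against RBD and NP arise after a natural COVID-19 infection". Anti-RBD is also the measure of vaccine response. The NP assay is included to tell the two sources apart, but the correlate analysis does not mention it.
- **Study participants.** A history of COVID-19 does not exclude a patient.

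**The concern.** A correlate of protection asks whether antibody present at a given time predicts infection after that time. At month 6 the plan forms groups by whether COVID-19 occurred, not by whether it occurred after the sample. A patient infected in month 3 is then a case whose month-6 anti-RBD partly results from that infection. The outcome has changed the predictor, which is reverse causation. If low antibody truly raises risk, cases should have lower titres than non-cases. Early cases with infection-induced antibody pull the case mean up and shrink that gap.

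At stake is whether the study can say that antibody level still matters half a year after vaccination. The Discussion presents the link between antibody level and protection as a main product of the study, so a month-6 result pushed towards no association could mislead.

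**Working it through.** The article gives no event rate, effect size or antibody distribution for this analysis, so there is no planned figure to reproduce. The check has two parts: how many cases precede each sample, and what that does to the difference in means.

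**1. Share of cases before each sample**

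Inputs from the article: two-year follow-up from dose 2 (730.5 days), and samples at day 28 and month 6 (182.6 days).

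- Share of the window: 28/730.5 = 3.8% and 182.6/730.5 = 25.0%.
- At constant hazard with two-year attack rate A, the share of cases before fraction f of the window is [1 - (1 - A)^f]/A.
- Month 6: A = 5% gives (1 - 0.95^0.25)/0.05 = 25.5%; A = 20% gives (1 - 0.80^0.25)/0.20 = 27.1%.
- Day 28: 3.9% and 4.3%.
- Simulation in which the hazard also varies with titre gives about 26-29% at month 6 and 4-5% at day 28.

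**2. Effect on the mean difference (cases minus non-cases)**

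Assumptions, none from the article: normal log10 titre with standard deviation s, log-linear hazard, infection adding b log10 to anti-RBD in everyone infected before the sample.

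- Without contamination, for a fairly rare outcome, the difference is D = s² × ln(HR per log10), which equals s × ln(HR per SD).
  - s = 0.5, HR 0.5 per log10: 0.25 × (-0.693) = -0.17.
  - s = 0.5, HR 0.3 per log10: 0.25 × (-1.204) = -0.30.
  - s = 0.6, HR 0.6 per SD: 0.6 × (-0.511) = -0.31.
- If a share p of cases precedes the sample, the planned comparison estimates about D + p × b. The sign reverses once b exceeds |D|/p.

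Simulated month-6 differences in log10. Landmarked means that only infections after the sample count and patients infected earlier are removed.

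| Setting | p | b | Landmarked | As written |
|---|---|---|---|---|
| HR 0.6 per SD, s 0.6, constant hazard | 26-28% | 0.3 | about -0.31 | -0.24 |
| same | 26-28% | 0.5 | about -0.31 | -0.19 |
| same | 26-28% | 1.0 | about -0.31 | -0.05 |
| same | 26-28% | 1.5 | about -0.31 | +0.08 |
| HR 0.5 per log10, s 0.5, A 5%, constant hazard | 26% | 0.3 | -0.17 | -0.09 |
| same | 26% | 0.5 | -0.18 | -0.05 |
| same | 26% | 1.0 | -0.17 | +0.08 |
| HR 0.3 per log10, s 0.5, A 5%, constant hazard | 26% | 1.0 | -0.30 | -0.05 |
| HR 0.5 per log10, A 5%, half the hazard before month 6 | 50% | 1.0 | -0.16 | +0.33 |
| HR 0.3 per log10, A 5%, half the hazard before month 6 | 51% | 1.0 | -0.30 | +0.21 |
| HR 0.5 per log10, A 5%, 10% of the hazard before month 6 | 11% | 0.3 | -0.18 | -0.15 |

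The short formula agrees. For the seventh row, -0.17 + 0.256 × 1.0 = +0.08. Break-even boosts at constant hazard are 0.17/0.256 = 0.66 log10 (HR 0.5 per log10) and 0.31/0.27 = 1.15 log10 (HR 0.6 per SD).

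**3. Day 28**

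With p = 4%, HR 0.5 per log10 and b = 1.0, the estimate is -0.174 + 0.04 × 1.0 = -0.134 (simulated -0.135). Reversal would need b above 0.174/0.04 = 4.4 log10. Across the s = 0.5 scenarios, including front-loaded infection, the as-written day-28 difference stays between -0.10 and -0.32. It is attenuated and never reversed.

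**The case against.** - **The wording can be read as forward-looking, and this is a condensed article.** To develop COVID-19 may mean after the sample, and the second-dose start date is stated for the primary endpoint. A fuller plan may set a landmark. This has some weight, but the article fixes the groups, sampling times and test, and carries the day-28 comparison over to month 6 unchanged. Nothing written sets the temporal order.
- **The dual assay separates infection from vaccination.** It could, but the correlate analysis does not use it. NP positivity also shows that infection occurred, not when.
- **The boost is an assumption.** This stands. The article says infection induces anti-RBD. It does not say by how much infection raises titres in vaccinated kidney patients. A reader might infer that reversal is to be expected, but that needs a large boost, front-loaded infections or a weak true association.
- **The surrogate cut-off is not at risk in the same way.** This also stands. A reader might infer that the announced correlate of protection could come out with the wrong sign. The cut-off uses day 28 only, where about 4% of cases precede the sample.
- **Related complaints are smaller or unquantified.** Choosing and reporting a Youden cut-off on the same data is optimistic, but with 4,000 per group and HR 0.6 per SD the apparent and true indices are 0.232 and 0.217 at 20% incidence, and 0.229 and 0.199 at 5%. The article gives no basis for sizing the effect of pooling patients with prior infection. It says only that non-responders can be offered a booster, and booster dates are not shown to be collected.

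**Conclusion.** The concern holds for the month-6 comparison. Followed as written, the plan counts patients infected before the sample as cases, about 26-29% of two-year cases at constant hazard, and compares titres that their infection has affected. If infection raises anti-RBD, the bias is always towards no protection. It ranges from minor (-0.15 against -0.18 log10 with few early infections and a small boost) through substantial (-0.19 against about -0.31 with a 0.5 log10 boost) to a hidden or reversed association under a large boost or front-loaded infections. These sizes rest on assumed effect, boost and timing, none of which the article states. The day-28 comparison and its cut-off are attenuated slightly and not reversed. This should be fixed; it does not invalidate the announced cut-off.

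**What to change.** In Efficacy - Antibody response, state for each of the two samples that:

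1. follow-up for this analysis starts on the sampling date;
2. only COVID-19 with onset after that date counts;
3. patients with reported or registry COVID-19, or NP positivity, at or before the sample are excluded or analysed separately. This includes infection before vaccination.

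These three rules remove the bias, whichever test is kept. Preferably, also use the cause-specific Cox approach already planned for the primary endpoint, with log antibody as a continuous predictor, so that death and unequal follow-up are handled consistently. Report the day-28 cut-off with internally validated performance (bootstrap or cross-validation).

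The cost is analysis wording and fewer cases in the month-6 comparison. NP results are already planned. Dates of COVID-19 onset are needed to place infections before or after the sample; where only NP positivity is available, it supports exclusion at the sample but not dating.

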### Study participants

The study population includes a subset of patients with CKD stages G4-G5 and patients on KRT in the Netherlands. The inclusion and exclusion criteria are mentioned in Table 1. Of note, patients will be eligible whether they have a history of COVID-19 or not.

**Table 1 Tab1:** Inclusion and exclusion criteria

*Inclusion criteria*	
1. Age of 18-80 years 2. Capable of understanding the purpose and risks of the study, to be fully informed and to give informed consent 3. Either - eGFR < 30 ml/min/1.73m^2^ but not on dialysis or with a kidney transplant - Haemodialysis or peritoneal dialysis - Kidney transplant recipient at least 6 weeks after transplantation	
*Exclusion criteria (≥ 1)*	
•Patients who opted out for the national dialysis (RENINE) and kidney transplantation (NOTR) registries.	

*eGFR* Estimated glomerular filtration rate

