### Patient characteristics

The patient characteristics that will be obtained are listed in Table 2.

**Table 2 Tab2:** Patient baseline characteristics

*General*	
• Age • Sex • BMI	
*Renal disease*	
• Primary kidney disease • Dialysis modality • Type of kidney transplantation.	
*Laboratory parameters*	
• Serum creatinine (μmol/L), eGFR (ml/min1.73m^2^), except in dialysis patients • Urine creatinine (g/L), urine protein (g/L) or albumin (g/L), except in dialysis patients • HbA1c (mmol/mol)	
*Intoxications*	
• Smoking, alcohol	
*Comorbidity*	
• Coronary heart disease / PCI / CABG • Heart failure • Hypertension • Peripheral arterial disease and/or abdominal aortic aneurysm • Cerebrovascular accident • Dementia • Lung disease • Liver disease • Diabetes • Cancer • HIV	
*PROMs*	
• SF-12 and DSI in the subset of dialysis patients	
*Medication*	
• Antihypertensive drugs • Steroids or other immunosuppressive agents	
*COVID-19*	
• COVID-19 and severity before vaccination	

*BMI* Body Mass Index, *eGFR* estimated Glomerular Filtration Rate, *HbA1c* Haemoglobin A1c, *PCI* Percutaneous Coronary Intervention, *CABG* Coronary Arterial Bypass Grafting, *HIV* Human Immunodeficiency Virus, *PROMs* Patient Reported Outcome Measures, *SF-12* 12-item Short Form health survey, *DSI* Dialysis symptom index, *COVID-19* Coronavirus disease 2019

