Nonetheless, the LESS CoV-2 study will provide key information with regards to the efficacy of SARS-CoV-2 vaccines in high-risk kidney patients. Antibody response data and clinical endpoints will be collected in a large cohort of patients of whom patient characteristics uniformly are obtained in national registries with almost complete coverage. All high-risk kidney patient groups are represented in the study. As such, the study will be sufficiently powered to identify patients’ characteristics and the humoral antibody response predisposing for COVID-19 breakthrough infection. Our study can serve as a template for other studies of vaccine efficacy in high-risk populations including the admission of digital informed consent and finger prick blood sampling at home. Harmonizing the design of vaccination studies will allow international comparison of larger datasets.

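### The link between antibody level and protection is tested by an unadjusted two-sample comparison, although prior infection, age and immunosuppression can create or mask it

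*Protocol article*

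**What the plan says.** Under Efficacy - Antibody response, the Protocol article states that the association between antibody response and protection "will be examined for each patient group separately". Antibody response at day 28, and again at month 6, is compared between patients who do and do not develop COVID-19: "We will examine this by use of the t-test or if more appropriate a non-parametric test". A logistic model with Youden's index follows, from which "a cut-off in the antibody response at 28 days will be defined to serve as a correlate of protection against COVID-19". No covariate is named in either step.

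The same section adjusts elsewhere. For the comparison of responders between patient groups: "In subsequent sensitivity analyses we will perform multiple regression analyses correcting for possible differences in age and sex between the patient groups". In transplant recipients it asks whether "the different immunosuppressive regimens are associated with response rate".

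Study participants notes that "patients will be eligible whether they have a history of COVID-19 or not". Table 2 collects "COVID-19 and severity before vaccination", together with age, sex, comorbidity and immunosuppressive agents.

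**The concern.** Antibody level is not randomised, so a difference between cases and non-cases reflects who has high antibodies as well as what antibodies do. The article supplies one confounder itself. Antibody measurement says that natural infection produces anti-RBD antibody, which is the quantity being compared. Earlier infection may also protect by routes that this assay does not see, and the Discussion concedes that only the humoral response is studied. Age and immunosuppression can likewise affect both antibody level and infection risk. All three vary within a patient group, so analysing the groups separately removes only the differences between groups.

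At stake is how the result will be read. The Discussion expects a threshold that predicts protection and helps to establish surrogate endpoints for new vaccines. It also asserts that "the study will be sufficiently powered to identify patients’ characteristics and the humoral antibody response predisposing for COVID-19 breakthrough infection". A surrogate for vaccine-induced protection should not rest on a comparison that mixes infection-derived with vaccine-derived antibody.

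**Working it through.** **What adjusts for what.**
- Multivariable Cox regression (age, sex, comorbidity, modality, immunosuppression) appears under Analysis of primary endpoint and serves the incidence comparisons.
- The repeat by evidence of prior infection is in the same subsection and refers back to those analyses.
- The age and sex correction serves the comparison of response between patient groups.
- Immunosuppressive regimen is examined as a predictor of response.
- The NP assay is measured to separate infection from vaccination but is not used in the antibody-protection comparison.

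None of these reaches the test in question.

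**Size if prior infection confounds.** The article gives no event rate, SD, alpha or power for this analysis, so there is no figure to reproduce. From the article (Study enrolment): n = 4000 per group. Assumed: two-sided 0.05; 10% two-year risk in patients not infected before; log10 titre SD 0.6; no effect of titre; prior infection in a share p, raising titre by s and carrying its own hazard ratio HR.

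Example: p = 0.10, s = 1, HR = 0.3.
1. Risk after prior infection: 1 - 0.9^0.3 = 0.0311.
2. Share of cases: 0.9 x 0.10 + 0.1 x 0.0311 = 0.0931, so 372.4 cases and 3627.6 non-cases.
3. Prior infection among cases: 0.1 x 0.0311 / 0.0931 = 0.0334. Among non-cases: 0.1 x 0.9689 / 0.9069 = 0.1068.
4. Spurious difference: d = s x (0.1068 - 0.0334) = 0.0734 log10.
5. Variances: 0.36 + 0.0334 x 0.9666 = 0.3923 (cases) and 0.36 + 0.1068 x 0.8932 = 0.4554 (non-cases).
6. True SE: sqrt(0.3923/372.4 + 0.4554/3627.6) = 0.0343. SE used by the pooled t-test: pooled variance 0.4495, so sqrt(0.4495 x (1/372.4 + 1/3627.6)) = 0.0365.
7. False-association rate: Phi((0.0734 - 1.96 x 0.0365)/0.0343) = Phi(0.05), about 52%. The unequal-variance t-test gives Phi(0.0734/0.0343 - 1.96) = Phi(0.18), about 57%.

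The same formulas (pooled test, both tails counted) give:

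| Shift s | HR | p = 5% | p = 10% | p = 15% |
|---|---|---|---|---|
| 1.0 | 0.3 | d 0.037, 19% | d 0.073, 52% | d 0.108, 81% |
| 1.0 | 0.5 | d 0.026, 11% | d 0.051, 28% | d 0.074, 49% |
| 0.5 | 0.3 | d 0.019, 9% | d 0.037, 19% | d 0.054, 34% |
| 0.5 | 0.5 | d 0.013, 7% | d 0.025, 12% | d 0.037, 19% |

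Simulation agrees. With s = 1 and HR 0.3 it gave about 53% at p = 10% and 81% at 15%. With HR 0.3 it gave 9-17% at p = 5% over the two shifts, and 9-35% with s = 0.5 over the three prevalences. A logistic model adjusted for prior infection rejected in about 2.5-8% of simulated studies, close to the nominal 5% given simulation error of 1 to 1.5 points.

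**Size if immunosuppression or age confounds.** Simulated with 200 studies per scenario, n = 4000, all other inputs assumed.
- Masking: true antibody odds ratio 0.8 per SD; 70% immunosuppressed, with antibody lower by 1.5 SD and infection odds ratio 0.5. The crude odds ratio moves to 0.93 and the t-test detects the effect in about 35% of studies. The adjusted model recovers 0.80 and detects it in 96%.
- Age: no true effect, antibody lower by 0.3 SD and infection odds ratio 0.7 per SD of age. The t-test is significant in 52% of studies, with higher antibody in cases.
- A strong true effect (odds ratio 0.7) is still found when immunosuppressed patients have lower infection risk (odds ratio 0.7 or 0.5), but it is attenuated to 0.75-0.81.

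**The case against.** **Prior infection is not overlooked.** The NP assay is there to tell infection from vaccination, and the primary analyses are repeated by prior-infection status. A reader might infer that the study ignores prior infection altogether. The documents do not support that; the gap is confined to this comparison.

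**The cut-off is a separate step.** A reader might infer that the t-test feeds the threshold, or that the threshold is known to be unadjusted. Neither is supported. The threshold comes from a logistic model that takes nothing from the t-test. Its covariates are unstated, and an article commonly leaves such a list to a fuller document. Only the two-sample test is unadjusted by its nature.

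**Prediction needs no adjustment.** This stands for a threshold used only to classify patients. It does not cover the surrogate-endpoint use in the Discussion.

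**The rejection rates look worse than the bias.** This stands too. With 4000 patients, differences of 0.01-0.11 log10 against an SD of 0.6 become significant. In the prior-infection scenarios the simulated AUC is only 0.505-0.540 and the maximum Youden index 0.01-0.07. A threshold resting on that alone would hardly discriminate, so a convincing but wholly false threshold is not to be expected from these inputs.

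**It is a secondary analysis, already split by patient group.** True, and the primary endpoint is unaffected.

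**Conclusion.** The point holds for the association test. The article fixes a method that cannot carry covariates, in a setting where it names a shared source of antibody and possible protection and already collects what is needed to adjust. That bias is possible follows from the design; its size does not. With a prior-infection hazard ratio of 0.3 and no titre effect, false association ranges from about 9% (5% prior infection, 0.5 log10 shift) to about 80% (15%, 1 log10 shift). It is smaller with a weaker prior-infection effect. Masking is equally possible if patients with low antibody also have lower infection risk. Every input except n = 4000 is assumed.

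A reader might go further and conclude that the study will report a false correlate of protection, or that its claim of adequate power is refuted. The documents support neither: prior-infection prevalence is not given, the spurious differences are small, and no power figure is stated to test. The change is worthwhile and inexpensive; it is not a fault in the primary analysis.

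**What to change.** Within each patient group, make the main association analysis a Cox regression of COVID-19 on log day-28 antibody, in line with the primary endpoint. Adjust it for prior infection (history and NP status), age, sex, comorbidity and immunosuppressive agents. Keep the t-test or non-parametric test as descriptive. Do the same at month 6, counting only COVID-19 that occurs after that sample, since an earlier infection would itself raise the month-6 level.

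An adjusted Cox model does not by itself yield one threshold. Derive the Youden cut-off in patients without evidence of prior infection, and state which covariates, if any, the logistic model contains. Describe an unadjusted cut-off as predictive only, not as support for a surrogate endpoint.

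The cost is analysis wording, as the covariates are in Table 2 and the NP assay is already planned. Missing covariates will need handling, the models carry a few more parameters, and the cut-off rests on a somewhat smaller sample.
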